## Discussion

EPIC-NSW is a population-based implementation trial of primary HIV prevention with daily TDF/FTC in the context of sexual HIV exposure. This trial evaluates the population impact of PrEP on the HIV epidemic in the entire state of NSW, Australia. It is distinct from studies which have examined the individual-level preventative effect of TDF/FTC [14].

Internationally, this is one of the first trials which aims to provide PrEP to the entire estimated population of GBM at high risk for HIV infection in a particular jurisdiction. EPIC-NSW follows the NSW PrEP guidelines [24] in identifying individuals at high risk for HIV infection. A targeted high-risk approach can be a viable and cost-effective option in other similar settings with initially limited access to PrEP.

The criteria for PrEP eligibility in EPIC-NSW take into account the local epidemiology of HIV acquisition [4, 39]. Factors with HIV incidence of about 2 per 100 person-years or higher were selected to indicate high risk for HIV acquisition in the Australian context. Indicators from the ongoing behavioral surveillance and other research in local gay communities [30, 32], which measure these criteria, were used to estimate the size of the population of GBM and, specifically, of the group at high risk of HIV which is targeted with PrEP.

The data systems employed in EPIC-NSW allow data to be linked between clinical health services in NSW and with NSW HIV notifications data. The methodology employed allows calculating HIV incidence not only in the EPIC-NSW cohort, but also diagnoses in the underlying population in the state of NSW. This methodology minimizes the data collection burden on health services and is as close to real life as possible. This makes EPIC-NSW one of the first population-based cohorts with an ability to assess the impact of PrEP at the population level.

With a follow-up time of at least 7400 person years, the study presents a unique opportunity to inform the international community about the additive effect of PrEP in HIV prevention.

This trial became possible due to the concerted efforts of the research team at the Kirby Institute, UNSW Sydney, the state government with its time-limited and goal-oriented HIV strategy [10], consensus from clinicians that PrEP implementation was required, a highly functional network of public and private health services, and community activism, leadership and participation in HIV prevention.

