## Background

In New South Wales (NSW), Australia, research findings in HIV treatment as prevention [1] were followed in 2012 by a state-wide HIV strategy that had an over-arching aim of working towards the virtual elimination of HIV by 2020 [2]. In response to widespread implementation of policy actions directed towards HIV treatment as prevention [3], HIV testing rates and ART coverage among people diagnosed with HIV have increased considerably. By 2015, an estimated 93% of people with HIV in NSW were diagnosed; 89.3% of those diagnosed were on treatment, of which 91.3% had suppressed viral load over the preceding 12 months [4–6]. However, by the end of 2015, new HIV diagnoses in NSW had not declined substantially, and more than 80% of diagnoses continued to be in gay and bisexual men (GBM) [7]. Undiagnosed, and thus untreated, HIV infections among GBM [8], combined with increasing levels of condomless anal intercourse with casual partners [9], continued to drive the HIV epidemic despite very substantial increases in HIV testing and treatment. In order to achieve a significant reduction in new HIV diagnoses, additional strategies were required. In this context, the NSW HIV Strategy 2016–2020 proposed the population-level roll-out of HIV pre-exposure prophylaxis (PrEP), in combination with strengthening condom use, testing, and treatment, in order to move forward towards the ambitious goal of virtually eliminating HIV transmission by 2020 [10].

PrEP, in the form of combined tenofovir disoproxil fumarate 300 mg (TDF) and emtricitabine 200 mg (FTC), is effective for primary HIV prevention [11–13]. TDF/FTC has a favorable safety profile [14] and effectively penetrates the anorectal mucosa [15–17], which makes it an ideal prophylactic agent for GBM. PrEP efficacy is closely related to adherence [14], and adherence has been higher in people who are well-informed about HIV and PrEP [12, 13, 18]. TDF/FTC is now recommended as PrEP for people at high risk of HIV acquisition in national or regional guidelines in the US, Europe and Australia [19–21], as well as by the WHO guidelines globally [22].

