### Study design

EPIC-NSW is a prospective observational study of PrEP roll-out, implementation and impact. It is an open-label, single-arm, multi-centre trial, undertaken by a multidisciplinary team led by the Kirby Institute, UNSW Sydney. The target population is predominantly GBM at high risk of HIV acquisition through sexual contact. However, other high risk individuals who are eligible for PrEP under the NSW PrEP guidelines can also enrol in the study (see Table 1).

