### Study endpoints

The primary focus of this study is on evaluating the population-level impact of a rapid, targeted PrEP roll-out on HIV diagnoses among GBM in the EPIC-NSW cohort, and HIV incidence among PrEP study participants. Table 4 presents key endpoints alongside study objectives.

**Table 4 Tab4:** Study objectives and endpoints

Study objectives	Endpoints
Primary	
i. Assess the incidence of HIV among PrEP study participants	i. Incidence of HIV infection per 100 person-years among study participants
ii. Measure the population-level impact of the rapid roll-out of PrEP on HIV diagnoses among GBM in NSW over a two-year period	ii. The annual number of HIV diagnoses among gay and bisexual men notified to the NSW Ministry of Health in the 12 months following full study enrolment
Secondary	
iii. Evaluate the rate of PrEP uptake among high risk GBM in NSW	iii. Rate of enrolment to the study by clinic type and clinic location
iv. Assess the incidence of STI (gonorrhoea, chlamydia and infectious syphilis) among people prescribed PrEP	iv. Incidence of STI (gonorrhoea, chlamydia and infectious syphilis) per 100 person-years among study participants
v. Describe patterns of PrEP use and medication adherence to the recommended PrEP medication schedule in those prescribed PrEP	v. Patterns of daily TDF/FTC PrEP use and adherence to the medication schedule among study participants (those who opted into brief surveys about adherence and risk behaviour

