#### Clinical data collection

All clinical data required to evaluate the uptake and impact of EPIC-NSW is sourced from routine electronic records maintained in the clinical patient management systems. A software program called GRHANITE is used to extract the data. The software was specifically developed to link primary care and hospital data without any personal information leaving the clinic and the tool is used in the ACCESS project [28], to extract and link data from primary care clinics, hospitals and laboratories [38]. Using GHRANITE, data are stripped of any identifying information before leaving the clinical site but can be linked by the scrambled client ID generated by the GHRANITE tool. EPIC-NSW study variables are regularly extracted from clinic databases, and transferred to the ACCESS central database at the Kirby Institute, UNSW Sydney. The variables extracted are: year of birth, country of birth, postcode of residence, Indigenous status, issuing of PrEP prescriptions, STI, HIV, hepatitis and creatinine clearance tests and test results, along with the scrambled client ID and clinic ID. The scrambled client ID is formed by the same conversion process as in the enrolment database. Each quarter, a list of scrambled client IDs from the EPIC-NSW enrolment database are provided to the ACCESS data custodians who retrieve the relevant EPIC-NSW study variables described above. The participating clinics utilising data management systems not compatible with GHRANITE enter the same clinical data in a secure online database developed in SurveyGizmo, and so that information from all clinics is available for monitoring of key indicators.

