### Data analyses

Using data from the EPIC-NSW cohort, we will calculate the incidence of HIV infection per 100 PY after TDF/FTC prescription and the effect-modifying role of non-adherence to the prescribed daily medication schedule. Incident infection is defined as an HIV diagnosis following a negative test, and time at risk calculated as the time between each patient’s first and last test or a patient’s first test and HIV diagnosis. The number of incident infections will be divided by the total person-years at risk. Analyses of HIV seroconversions will also include a period of 12-months after the completion of the study treatment, using data linkage with the NSW HIV registry (for those participants who consent to data linkage). Similarly, we will calculate the incidence per 100 PY for gonorrhoea, chlamydia and syphilis. Comparisons of incident events across groups and over time will be conducted using survival analysis and cox proportional hazards regression methods.

Using routinely available HIV and STI surveillance data in NSW, we will also assess the average quarterly trends of HIV and STI tests and diagnoses in the population, including in the 12-month period immediately prior to the commencement of recruitment (the pre-intervention period), compared to the 12-month period immediately after the recruitment of the sample of 3700 high-HIV risk individuals.

Analyses of sexual practices and adherence to PrEP will be conducted on the subsample of GBM participating in the optional adherence and behavioural survey. Analyses of sexual practices will mainly focus on CLAI. Analyses of adherence to the study medication will concentrate on time on PrEP, proportion and count of days when PrEP pills were taken, temporal changes in CLAI and PrEP use, and the relationship between CLAI and adherence. We will use longitudinal regression methods as appropriate for binary and count data analyses, to compare proportions and counts of events between groups and to assess trends in proportions and event counts over time.

The study Management Team monitors the study enrolment and primary study outcomes against new HIV diagnoses notified to NSW Health and reported each quarter.

Data analysis is conducted by the Kirby Institute research staff using STATA (StataCorp, College Station, TX, USA).

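### The before-after change in NSW diagnoses cannot isolate PrEP, because condom use, testing and treatment are strengthened under the same strategy and nothing in the stated comparison separates them

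*Protocol article*

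**What the plan says.** All references are to the protocol article.

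- **Background.** Under the 2016–2020 strategy, PrEP is introduced "in combination with strengthening condom use, testing, and treatment, in order to move forward towards the ambitious goal of virtually eliminating HIV transmission by 2020". The same section reports high and rising testing and treatment before 2016, diagnoses that had not fallen substantially by the end of 2015, and more condomless sex with casual partners.
- **Study design.** "It is an open-label, single-arm, multi-centre trial, undertaken by a multidisciplinary team led by the Kirby Institute, UNSW Sydney". There is no concurrent comparison group.
- **Study endpoints, Table 4.** Primary objective ii is to "Measure the population-level impact of the rapid roll-out of PrEP on HIV diagnoses among GBM in NSW over a two-year period". Its endpoint is the annual count of notified GBM diagnoses in the 12 months after full enrolment.
- **Data analyses.** Quarterly trends in HIV and STI tests and diagnoses in the 12 months before recruitment are "compared to the 12-month period immediately after the recruitment of the sample of 3700 high-HIV risk individuals". No control population, covariate adjustment or modelled counterfactual is named.
- **Discussion.** The trial is said to evaluate what PrEP does to the epidemic across the whole state. A later sentence, which opens with follow-up of at least 7400 person-years (PY), says that "the study presents a unique opportunity to inform the international community about the additive effect of PrEP in HIV prevention".

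**The concern.** An additive effect is what PrEP contributes beyond condoms, testing and treatment. To estimate it, those three must be held fixed or accounted for. The Background says they are to be strengthened under the same strategy that introduces PrEP, and the stated contrast is simply before against after. It therefore answers how diagnoses changed while PrEP was rolled out as part of a package.

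What is at stake is the reading of a co-primary result that is explicitly offered to other jurisdictions. If treatment or condom gains contribute to a fall, those jurisdictions would expect too much from PrEP alone. If wider testing finds more existing infections, or condomless sex keeps rising, a real PrEP effect could look small or absent.

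**Working it through.** **1. Claim, co-interventions and comparison side by side**

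| Element | Where | Content |
|---|---|---|
| Claim | Table 4 objective ii; Discussion | Impact of PrEP on NSW diagnoses |
| Co-interventions | Background | Condom use, testing and treatment strengthened under the same strategy |
| Comparison | Data analyses | 12 months before recruitment against 12 months after the 3700 are recruited |
| Control or adjustment | Data analyses | None stated; HIV tests are tracked, but no step uses them to adjust diagnoses |

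**2. Does the cohort endpoint supply the missing comparator?**

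The only power figure, in the Participants section, is 99.2% for a 50% reduction from 1.8 per 100 PY. Inputs: 3700 participants and 80% retention, so n = 3700 × 0.80 = 2960; p0 = 0.018; p1 = 0.009. Alpha is not stated; two-sided 0.05 is assumed.

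- Power = Φ{[p0 − p1 − 1.96·√(p0(1 − p0)/n)] / √(p1(1 − p1)/n)}
- = Φ{[0.009 − 1.96 × 0.002444] / 0.001736} = Φ(2.43) = 99.24%

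The stated figure is reproduced as a one-sample test against a fixed historical rate. A two-group test with 2960 per group gives 85.1% and does not reproduce it. So the cohort endpoint is also judged against the past, and neither co-primary endpoint has a concurrent comparator.

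**3. What the before-after contrast would show (illustration)**

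Let P be the true proportional fall due to PrEP and C the proportional fall due to everything else; C is negative if other influences raise diagnoses. Observed fall = 1 − (1 − P)(1 − C). P and C are assumed, since the documents give neither. With P = 20%:

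| C | Observed fall |
|---|---|
| 40% | 1 − 0.80 × 0.60 = 52% |
| 20% | 1 − 0.80 × 0.80 = 36% |
| 0% | 20% |
| −10% | 1 − 0.80 × 1.10 = 12% |
| −20% | 1 − 0.80 × 1.20 = 4% |

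With P = 0 and C = 20% the observed fall is 20%, the same as for a pure 20% PrEP effect.

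**4. Room for treatment gains**

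The Background gives 93% diagnosed, 89.3% of those treated and 91.3% of those suppressed for 2015. 0.93 × 0.893 × 0.913 = 0.758, so 24.2% are not suppressed. Under assumed later values:

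| Diagnosed / treated / suppressed (%) | Unsuppressed | Relative fall from 24.2% |
|---|---|---|
| 93 / 92 / 93 | 20.4% | 15.5% |
| 95 / 92 / 93 | 18.7% | 22.6% |
| 95 / 95 / 95 | 14.3% | 41.0% |

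These are falls in the unsuppressed share, not in diagnoses. They show only that the room for change is not negligible.

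**5. What the cohort could directly account for**

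Infections directly averted = (1.8 per 100 PY − observed cohort incidence) × cohort PY. With the 84% reduction cited in the Participants section, cohort incidence would be 1.8 × 0.16 = 0.288 and the difference 1.512 per 100 PY. Over one year that gives 29.6 × 1.512 = 44.8 infections at 2960 PY and 37.0 × 1.512 = 55.9 at 3700 PY. With complete protection the figures are 53.3 and 66.6. They lean low: the article describes incidence as above 1.8, 3700 is a minimum enrolment, and onward infections averted are left out.

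**The case against.** The strongest reply is the history. Testing and treatment rose from 2012 while diagnoses stayed roughly flat, so a fall that appears once PrEP arrives is naturally read as PrEP. This carries some weight, but only as an informal counterfactual. The Background explains the flat trend by undiagnosed infection and rising condomless sex, which the strengthened testing and condom components address, and the planned comparison uses only 12 months of pre-period. Nor do the documents say when, or by how much, the other components step up. They may merely continue their earlier rise, in which case a longer pre-series would help.

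A second reply is that adjustment belongs in the full protocol or SAP, and that a state-wide roll-out cannot have a control arm. Both are fair, and the absence of modelling detail is not the point. The article itself fixes the comparison and attaches a PrEP-specific claim to it.

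Three stronger readings are tempting, and the documents support none of them.

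- A reader might infer that the plan assigns the whole change to PrEP. No sentence does so. The endpoint is a count, the analysis assesses trends, and the additive-effect sentence leans on cohort follow-up; the link to state diagnoses comes from objective ii and the rest of the Discussion. Single-arm person-years cannot show additivity either.
- A reader might infer that the bias must favour PrEP. More testing can raise diagnoses in the short run, and more condomless sex works against PrEP.
- A reader might infer that concurrent treatment gains would be as large as the PrEP effect. That comparison needs assumed later coverage, an annual GBM diagnosis count that the article does not give, and diagnoses falling in proportion to the unsuppressed share.

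**Conclusion.** The concern holds as a limit on interpretation. As stated, co-primary (ii) estimates the change in GBM diagnoses during PrEP roll-out within a combined strategy; it does not isolate PrEP. This follows from the article's text and needs no numerical assumption. The direction of bias is open and its size cannot be determined from the documents; the 4% to 52% range for a true 20% effect rests wholly on assumed inputs. No sample size or power figure changes, and neither the cohort incidence estimate nor the data collection is called into question. The point should be fixed because it governs what the trial may conclude, but it is not a fatal flaw.

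**What to change.** 1. **Wording.** In Study endpoints (Table 4), Data analyses and Discussion, describe the co-primary (ii) conclusion as the change in GBM diagnoses during PrEP roll-out under the combined strategy. Claim no additive PrEP effect from this contrast alone.
2. **Context.** Report the observed change beside the concurrent trend in HIV testing, which is already planned, and beside the treatment and suppression coverage that the Background cites for 2015, updated for the post-recruitment window.
3. **Plausibility check.** Report beside it the infections directly averted in the cohort: (1.8 per 100 PY with its uncertainty, minus observed cohort incidence) × cohort PY in the window. State that this omits onward infections, and that infections averted in a window are not the same as diagnoses averted in it. It must not serve as a cap on what is attributed to PrEP.
4. **Exploratory only.** Clinic extracts include "year of birth, country of birth, postcode of residence, Indigenous status, issuing of PrEP prescriptions", so uptake by area can be described. Compare high- and low-uptake areas only if notifications by area are also available, which the article does not say. Counts would be small, and high-uptake areas may also have stronger testing and treatment.

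The cost is a less sweeping claim, a few sentences of text and a little more analysis, including obtaining later treatment and suppression figures.

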## Abbreviations

FTC: Emtricitabine
GBM: Gay and Bisexual Men
HIV: Human Immunodeficiency Virus
HREC: Human Research Ethics Committee
NSW: New South Wales
PrEP: Pre-exposure Prophylaxis
PY: Person-years
STI: Sexually Transmitted Infection
TDF: Tenofovir Disoproxil Fumarate
